### Trial Groups

After randomisation, Essentia staff will be automatically guided through the correct intervention for each participant via four on-screen templates. The Essentia database will be configured so that only the template which corresponds to the appropriate treatment allocation can be used. Participants will be randomly allocated to either usual care (i.e. control group, called the 'Together Programme') which comprises reactive counselling or proactive counselling (intervention 1) as described below. Within these two groups there will also be random allocation of smokers to either being offered advice to obtain nicotine addiction treatment (i.e. NRT, Varenicline or Bupropion) from their general practitioner or local NHSSSs (control) or an offer of a voucher which can be redeemed at a pharmacy for a free supply of NRT (intervention 2). The aim is to have four trial groups of equal size.

### Control – Together Programme

Usual Together Programme care involves offering smokers support with smoking cessation via telephone, email, written materials and/or text message and, if appropriate, advising them to seek further support (potentially including nicotine addiction therapies) from their local NHSSS or general practitioner. After their first session, participants will be contacted by telephone (unless they prefer email or text message) on their quit dates and at two days and three weeks afterwards with brief motivational messages.

### Intervention 1 – Proactive telephone counselling

Smokers will be offered usual "Together Programme" written materials and modified email and text messages, plus a programme of proactive telephone counselling following an agreed protocol, delivered by specially-trained Essentia counsellors. After their initial counselling session, participants will receive another call for counselling prior to their quit date and also on the day that they stop smoking itself. Subsequently participants will be eligible to receive up to 4 further telephone counselling sessions in the 3 weeks after their quit date. Earlier sessions will help smokers to focus on and prepare for quitting and later ones will focus on remaining smoke-free and preventing relapse. This call pattern is based on a previously-trialled, US quitline calls schedule and the weekly contacts made after smokers' quit dates follow a similar frequency to that used for face-to-face counselling by many NHSSSs. During counselling and, if appropriate, smokers will be advised to obtain further support (including, potentially, nicotine addiction therapies) from their local NHSSSs or general practitioners. [name] (UCL – a protocol author) will develop the intervention protocol and train counsellors in proactive telephone counselling.

### Intervention 2 – Provision of voucher for free NRT

During discussion of nicotine addiction treatments, callers will be offered a voucher which can be redeemed at a pharmacy for a cost free supply of NRT. Not all smokers will choose to accept the voucher. For example, some smokers might have previously used NRT, so that they do not believe using this again is likely to be effective. Others might prefer to try different treatments for nicotine addiction which can be obtained from other sources.

For smokers who choose to accept the offer of an NRT voucher, the Essentia counsellor will run through with them a checklist of cautions to NRT. This checklist will be identical to that which is in the product information that accompanies the over the counter (OTC) formulation of NRT used in the trial. If callers report uncertainties about any of the listed cautions applying to them, a voucher will not be issued and they will be advised to discuss the potential use of NRT with their GP. Vouchers will be generated electronically by the Essentia counsellor and sent to the pharmacy team responsible for voucher redemption and participants will be given a freephone number to call for voucher redemption. Confirmation of this number will sent by email, text or paper mail according to participants' preferences.

A 15 mg/16 hr transdermal nicotine patch which is available over the counter (OTC) and, hence, on the UK 'General Sales List' will be used and there are no specific recommendations regarding their purchase or storage. Although smokers in the UK can purchase such medication OTC, we propose that voucher redemption is overseen by a pharmacist to provide reassurance about trial safety. NRT will be stored securely within a Glasgow pharmacy and a secure system for recording i) when NRT has been issued against any one voucher and ii) the batch number of NRT sent to individuals will be used. The pharmacy team will be part of the NHS Greater Glasgow and Clyde's Public Heath Pharmacy Department.

Participants will be required to telephone the pharmacy team to redeem their voucher and obtain NRT and they will not be directly sent NRT without making such a request. Participants' vouchers will make them eligible for up to 6 weeks cost-free NRT treatment, supplied in batches. All NRT packaging and instructions will be identical to that which has been approved for retail sale on a General Sales License outside of pharmacies

In all trial groups, if smokers have not tried to stop on their agreed quit date and they still wish to stop smoking, a new (i.e. second) quit date will be agreed and the timing of follow-ups will be tied to this point but no further re-negotiation of quit dates will be permitted.

### Compliance

This is a pragmatic trial, testing the delivery of interventions in routine clinical use, using an intention to treat analysis. In such studies it is usual for participants to have variable compliance with interventions as their level of engagement with these is self selected. Consequently, uptake rates for interventions (e.g. the proportion of subjects who redeem NRT vouchers) are amongst study outcomes.

### Frequency and duration of follow up

Interim follow up will occur at one month and final follow up is at six months which is consistent with agreed standards for the measurement of smoking cessation outcomes in trials.[16] BMRB Social Research, a social research company, will contact trial participants to obtain follow up data. All participants will be asked about smoking outcomes and health status (EQ5D) and up to 10 attempts will be made to contact participants before they are categorised as 'lost to follow up'. Exhaled carbon monoxide readings will be used to assess smoking status amongst those smokers who report either i) continuous abstinence from smoking cessation between their quit date and 6 months, ii) 7 day (or longer) point prevalence abstinence from smoking at 6 months. BMRB staff will visit those smokers who report smoking cessation and obtain exhaled CO samples. A cut off point of 10 ppm of CO[16] in exhaled air will be used to differentiate between smokers and non-smokers and three attempts at CO validation will be made before any participant is recorded as non-contactable.

### Methods for protecting against bias

It will be impossible for Essentia staff delivering trial interventions to predict the outcome of randomisation, so there should be no bias in the allocation of participants to trial groups. All staff collecting follow-up information will be blind to participants' treatment allocations. As participants cannot be blinded to their allocated intervention, information about trial interventions will be carefully worded to ensure that this does not contribute to higher drop out rates in any one trial arm.

## Statistical Methods

### Sample Size and Justification

Sample size has been calculated to ensure that the trial is adequately powered to detect meaningful differences in the primary outcome measure (self report) and also in the secondary outcome that involves biochemical validation of this. A Cochrane review which compares, for smokers who call quitlines, proactive telephone cessation counselling with very brief counselling and/or the provision of smoking cessation materials only shows that proactive counselling is effective (OR = 1.41, 95%CI 1.27 to 1.57)[13]. Furthermore, there is evidence that telephone counselling is slightly more effective for motivated smokers (i.e. those prepared to make a quit attempt) [OR (in favour of motivated) 1.64, 95%CI 1.41 to 1.92] [13]. For the PORTSSStrial, we will assume that proactive counselling (compared to reactive) will have a treatment effect with an OR of 1.5. Given that we intend to recruit only motivated smokers to this study, however, this is probably a conservative assumption. The impact of telephone counselling is likely to be increased by the offer of NRT vouchers; two non-randomised US studies have shown that offering NRT (or NRT vouchers) in addition to standard quitline increased cessation rates at 6 months by 80% and 77% respectively[14,20]. A further randomised controlled trial with a factorial design assessed the impact of three levels of intensity of telephone counselling and of the offer of NRT and found an effect of NRT (OR = 1.58) and no evidence of interaction between the effects of counselling intensity and offer of NRT [21]. Consequently, we will assume that the offer of NRT vouchers is also associated with a treatment effect with an OR of 1.5, i.e. that the size of this effect is similar to that for proactive compared to reactive support, and that there will be no interaction between the effects of these two interventions.

Predicting control group (reactive support, no offer of NRT) quit rates for the PORTSSStrial is difficult because no previous UK trials have specifically enrolled motivated smokers (i.e. those who agree to make a quit attempt) and also previous trials have relied solely on self-report measures of smoking behaviour. Recruiting motivated smokers to PORTSSSis likely to increase quit rates at 6 months relative to previous UK trials, whereas using biochemical validation of smoking behaviour will probably diminish the number of cases for which primary outcome data is ascertained, apparently decreasing PORTSSS's quit rates. However, two recent UK trials with similar control group interventions to that proposed in PORTSSSreported, at 6 months, rates of prolonged abstinence from smoking for at least 3 months of 11.6%[19] and 9.0%[22], respectively. Consequently, we anticipate that in PORTSSS, self-reported prolonged abstinence between smokers' quit dates and their 6 month follow up will be 12% in the control group (reactive support, no offer of NRT). However, our experience shows us that up to 1/3 of participants who claim abstinence from smoking will not provide saliva samples at follow up, so we reduce the expected abstinence rate in the control group to 8%. In this factorial design, assuming no interaction between treatments, the comparison group for each treatment will comprise the combination of the control group (who receive neither treatment) and the group receiving only the other treatment (see Figure 2). For example, if the odds ratio for each treatment is 1.5 and the abstinence rate in the control is 8%, the comparison "group" would be expected to have an abstinence rate of 10% (i.e. the average of 8% and 12%). In the absence of interaction, we plan two a priori comparisons of the effect of each treatment versus the appropriate comparison group, using p < 0.05 as the level of statistical significance. Table 1 illustrates how variations in treatment effects and control group quit rates might affect the sample size required to have 80% power and 90% power (i.e. 90% chance of detecting a real effect caused by the trial intervention). Remember that in this table intervention and control groups are amalgamations of trial arms such that NRT versus no NRT and proactive versus reactive counselling are compared.

**Table 1 T1:** Sample sizes with different treatment effects and control group quit rates

Control (reactive support, no offer of NRT) group quit rate at 6 months (%)	Comparison "group" quit rate at 6 months (%)	Intervention "group" quit rate at 6 months (%)	Odds ratio for each treatment effect (proactive vs reactive, NRT vs no NRT)	Power	Required sample size per group (total for 4 groups)
12%*	14%	18.6%	1.4	80%	536 (2142)

12%*	14.5%	20.3%	1.5	80%	355 (1420)

12%	14.5%	20.3%	1.5	90%	468 (1872)

8%**	9.5%	12.8%	1.4	80%	739 (2956)

**8%****	**10%**	**14%**	**1.5**	**80%**	**489 (1956)**

**8%****	**10%**	**14%**	**1.5**	**90%**	**644 (2576)**

*** **self report quit rates, ** biochemically validated quit rates

Final row figures (bold) show our most likely estimates for required sample sizes.

**Figure 2 F2:**
[figure not shown]
**Comparison Groups within PORTSSS Trial**.

A further consideration is the increase in type 1 error arising as a result of including two primary treatment comparisons: proactive versus reactive counselling and NRT versus no NRT. A more conservative approach would adjust the p value to reflect the number of comparisons to be made i.e. take p = 0.025 (0.05/2). Table 2 shows the same power calculations as above using the more conservative p = 0.025.

**Table 2 T2:** Sample sizes with different treatment effects and control group quit rates using conservative 'p' value (0.025)

Control (reactive support, no offer of NRT) group quit rate at 6 months (%)	Comparison "group" quit rate at 6 months (%)	Intervention "group" quit rate at 6 months (%)	Odds ratio for each treatment effect (proactive vs reactive, NRT vs no NRT)	Power	Required sample size per group (total for 4 groups)
12%*	14%	18.6%	1.4	80%	644 (2576)

12%*	14.5%	20.3%	1.5	80%	426 (1704)

12%	14.5%	20.3%	1.5	90%	550 (2200)

8%**	9.5%	12.8%	1.4	80%	888 (3552)

**8%****	**10%**	**14%**	**1.5**	**80%**	**587 (2348)**

**8%****	**10%**	**14%**	**1.5**	**90%**	**760 (3040)**

*** **self report quit rates, ** biochemically validated quit rates

Final row figures (bold) show our most likely estimates for required sample sizes.

To allow for this more conservative analysis we should aim to recruit 3040 participants for 90% power. However, if we aim to recruit 2576 we would have 90% power to detect these differences as significant using a 5% significance level, and at least 80% power to detect these differences as significant at the more conservative 2.5% significance level.

### Planned recruitment rate

It should be feasible to recruit 2576 smokers in approximately 6 months, though this can only be confirmed after recruitment begins. In the first 6 months of 2007, 13,418 smokers registered with the Together Programme and the trial will recruit from this pool of callers. In a previous trial, only 28% of quit line callers who wanted counselling also agreed to trial enrolment[19] and our necessary requirement that participants agree to set a quit date could further reduce enrolment and randomisation rates amongst Together Programme registrations. Without piloting, one cannot be entirely certain about the proportion of callers who will agree to trial enrolment, but it is likely that this will be sufficient for recruitment.

### Potential problems with compliance

Participants randomised to receive proactive telephone support may not actually answer or be available for many of the calls that are made to them. If this situation were to arise, then it could attenuate any differences between interventions delivered to the control and intervention groups, making it harder to detect an effect attributable to the proactive call protocol. Additionally, participants who register for the Together Programme are currently able to telephone smoking cessation advisors whenever they wish and if a large number make such calls were to be made, this could further reduce differences between interventions. Consequently, treatment protocols in the reactive and proactive arms of the trial will need to be clearly defined.

### Expected rate of loss to follow-up

Previous UK studies have experienced losses to follow up in the region of 30%[19,22] and we have planned for a similar rate in this study, despite hoping to improve upon this by using a specially-commissioned market research company for follow up.

### Statistical Analysis Methods

Primary analysis will be by intention to treat, presuming continued smoking in those lost to follow-up. We will initially look for evidence of interaction between the effects of the two treatment interventions (proactive versus reactive support, and offer of NRT voucher versus no voucher offer) using a test of interaction in a logistic regression model. We do not anticipate interaction and presuming there is none, we will compare those who were randomised to proactive support (i.e. the combination of two groups) with those randomised to reactive support, and those offered of NRT with all those not offered NRT, using two distinct chi-squared tests (see Figure 2 below).

We will compare baseline characteristics of intervention and usual care groups, adjusting for any baseline differences using multiple logistic regression. We will carry out a sensitivity analysis to determine the influence of how missing data at follow-up are handled on the study conclusions, varying the strength of association between smoking status and 'missingness' (i.e. whether data are missing), and allowing for individual, sampling and imputation variation using multiple imputation.[23] We will investigate whether or not socio-economic deprivation (as measured by Townsend's score) is associated with successful outcome by looking for effect modification using a test for interaction to establish whether the effect of each treatment is similar in more versus less deprived groups. The data will be analysed at the end of the study only; there is no need for interim analyses on safety grounds, and having interim analyses alters the chance of type 1 or type 2 error.

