#### Randomisation process

All smokers who register with the 'Together Programme' will be eligible for trial enrolment and Essentia counsellors will randomise callers to one of four treatment groups after obtaining their informed consent. A computer programme will generate a random number sequence and, after randomisation, participants will be issued with a unique trial number and a code which corresponds to their treatment and the first session of the allocated treatment will be delivered. Any data that are exported for use by the research team will have the treatment allocation codes stripped out to maintain blinding. A key for the numerical code will be held by the trial statistician who will conduct the sole statistical analysis of trial data after the trial has ended.

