### Baseline Measures

Consent will be obtained to use the following data items which are routinely-obtained from all smokers who register with the Together Programme:

birth date, gender postcode, employment status, ethnic group, pregnancy, eligibility for free prescriptions, previous use of treatments for nicotine addiction, strength of nicotine addiction as measured by the 'heaviness of smoking index'[18] and quit attempts in the previous year.

Additionally, health status measured by EQ5D[17] will be ascertained and participants will agree a quit date for stopping smoking which is within four weeks. It is important that the quit date is agreed before randomisation because in a similar study, setting a quit date was not a criterion for trial entry and approximately 43% of those enrolled did not subsequently set one.[19] By requiring participants to set quit dates, we will ensure that only the most motivated smokers enrol into the trial and each participant will have a definite event from which subsequent counselling sessions and research follow ups can be timed.

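### Covariates for the adjusted logistic regression are chosen by observed baseline imbalance, and the plan does not say whether the adjusted or the chi-squared result leads

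*Protocol article*

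**What the plan says.** All of this is in the Protocol article.

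- **Main comparison.** Statistical Analysis Methods first tests the interaction of the two interventions in a logistic model. If there is none, it compares proactive with reactive support, and NRT offer with no offer, "using two distinct chi-squared tests". Sample Size and Justification calls these two comparisons a priori, "using p < 0.05 as the level of statistical significance".
- **Adjustment.** The next paragraph of Statistical Analysis Methods reads: "We will compare baseline characteristics of intervention and usual care groups, adjusting for any baseline differences using multiple logistic regression". It names no covariate and does not define a difference. It does not rank the adjusted result against the chi-squared result.
- **Data available.** Baseline Measures lists items taken before randomisation, among them "strength of nicotine addiction as measured by the 'heaviness of smoking index'[18] and quit attempts in the previous year". It then adds: "Additionally, health status measured by EQ5D[17] will be ascertained". Counting birth date, gender, postcode, employment, ethnic group, pregnancy, free-prescription eligibility, previous treatment use, heaviness of smoking index, previous-year quit attempts and EQ5D gives 11 items. None is named as an adjustment covariate. Townsend score appears only as a possible effect modifier.
- **Randomisation.** "A computer programme will generate a random number sequence"; no stratification factor is stated.

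**The concern.** The adjustment sentence is a selection rule: a variable enters the model because it happened to differ between groups. That is the wrong criterion. With concealed random allocation any difference is chance. A covariate earns its place by predicting the outcome, which imbalance does not show.

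Four things follow.

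1. The covariate set is unknown until the data are seen. The sections on blinding and randomisation say that the trial statistician holds the allocation key, conducts the sole analysis after the trial ends, and must identify treatment combinations during it. The choice could thus be made with outcomes and allocation both in view.
2. The sentence speaks of intervention and usual care groups, which does not map onto a 2x2 design with two pooled comparisons. Applied to each factor separately, it can give two different covariate sets.
3. Plausible predictors such as nicotine dependence would usually be left out, because they usually balance.
4. There will be two results per factor, with no stated order between them.

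At stake is how far the adjusted odds ratios can be trusted as fixed in advance, and what is reported if they and the chi-squared tests fall on different sides of 0.05.

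**Working it through.** **1. What the trial is sized on.** The inputs are a control rate of 8%, an odds ratio of 1.5 for each factor ("we will assume that proactive counselling (compared to reactive) will have a treatment effect with an OR of 1.5", and the same for NRT), no interaction, 90% power and two-sided 0.05.

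- Cells: 8%; 0.08/0.92 × 1.5 gives 11.54% (two cells); a further × 1.5 gives 16.36%.
- Margins: (8 + 11.54)/2 = 9.77% and (11.54 + 16.36)/2 = 13.95%.
- n per side = [1.96√(2p̄q̄) + 1.2816√(p₁q₁ + p₂q₂)]² / (p₂ − p₁)² = 1255, or 627.5 per group. With continuity correction it is 651. The stated 644 (total 2576) lies between them. The rounded 10% and 14% would give 692.5, so the stated figure rests on unrounded rates.

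The trial is therefore sized on the unadjusted marginal comparison, which no covariate choice can alter.

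**2. How often the rule would act.** The article does not define a difference. Assume p < 0.05 and independent items.

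- At least one of 11 items flagged for one factor: 1 − 0.95¹¹ = 43%.
- Over both factors: 1 − 0.95²² = 68%.
- With 8 to 12 items, one factor: 34% to 46%.
- Any one given predictor is flagged in about 5% of trials.

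The rule would thus often adjust for something, and rarely for a particular variable that matters.

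**3. Effect on error rates, one prognostic covariate.** Simulation with 2500 runs per setting, N = 2576, 10 independent covariates of which one is prognostic (assumed OR 1.5 or 2.0 per SD), and imbalance flagged at p < 0.05. The treatment effect is that of 10% against 14%: (0.14/0.86)/(0.10/0.90) = 1.465.

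| Prognostic OR per SD | True effect | Unadjusted | Imbalance-driven | Prespecified |
|---|---|---|---|---|
| 1.5 | none | 5.0% | 5.0% | 5.3% |
| 2.0 | none | 5.2% | 5.0% | 5.2% |
| 1.5 | OR 1.465 | 86.2% | 86.0% | 86.7% |
| 2.0 | OR 1.465 | 83.7% | 83.5% | 85.0% |

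The prognostic covariate was selected in 4.8% to 5.4% of runs. The Monte Carlo standard error is about √(0.86 × 0.14/2500) = 0.7 points for power. The paired differences between methods are tighter than that.

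**4. Several prognostic covariates and an open threshold.** A second simulation used 11 covariates, five of them prognostic (assumed log-OR 0.3 to 0.6 per SD). It compared no adjustment with adjustment for imbalances at p < 0.05, 0.10 or 0.20, since the wording permits any of these.

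- No effect: each analysis alone rejected in about 4.4% of trials. Reporting the most favourable of the four gave 5.5%.
- Significance depended on which of the four was chosen in 4.3% of trials at OR 1.5 and in 6.3% at OR 1.3.
- A fixed model with both factors and the prognostic covariates raised power from 85.2% to 87.8% at OR 1.5 (2.6 points) and from 47.5% to 51.1% at OR 1.3 (3.6 points). The imbalance-driven models gained essentially nothing.

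**The case against.** The strongest reply is that the leading comparison is already settled. Two a priori comparisons are named, their test is named, and the sample size tables rest on the same marginal proportions. This stands in part. The chi-squared results cannot be moved by covariate choice. But the article never says that the adjusted result is subordinate, so the order between them is inferred.

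A second reply is that a journal article leaves covariates to the analysis plan. That would excuse an absent list. It does not excuse a stated rule, because an analysis plan with fixed covariates would depart from this text.

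A reader might also infer several stronger things that the documents and the calculations do not support:

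- *That the selection step invalidates the confidence interval or inflates type I error.* The rejection rate under no effect stayed near 5% when a threshold was applied mechanically.
- *That 43% is an error rate.* It is the chance that some covariate enters, under a p < 0.05 test and an independence that the article does not state. Employment, free-prescription eligibility, age and postcode are plausibly related.
- *That the chi-squared tests lose by ignoring the other factor.* With the margins above, the marginal OR is (0.1395/0.8605)/(0.0977/0.9023) = 1.497 against 1.5, and the four groups are meant to be equal in size.
- *That the primary test must be replaced.* An adjusted primary analysis would change the target from a marginal to a conditional odds ratio. Curing the defect does not require that.

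**Conclusion.** The point holds for the adjusted analysis. The plan states a poor rule for choosing covariates, leaves their identity to be settled after the data are seen, and does not rank the adjusted result against the chi-squared result. The primary chi-squared tests remain prespecified and valid.

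The size is modest. There is no material type I inflation under a mechanical threshold. If the most favourable analysis were picked, the error rate rose by about one point (4.4% to 5.5%). A fixed prognostic set would bring roughly 0.5 to 3 points of power near the design effect. These figures rest on assumed prognostic strengths, since the article gives none for the heaviness of smoking index or any other item, and on independent covariates. The main gain from a change is an adjusted result fixed in advance. It is worth making because it costs little.

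**What to change.** In Statistical Analysis Methods:

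1. Delete the clause that adjusts for observed baseline differences.
2. Prespecify one logistic model containing both randomised factors and a short fixed list of covariates already collected. Examples are heaviness of smoking index, age, gender, previous-year quit attempts, and Townsend score, which that section already plans to use. Report each factor's odds ratio with its 95% confidence interval from this model.
3. State in advance which result leads. Either keep the chi-squared tests as primary with this model as the fixed adjusted analysis, or make the model primary.
4. Give a simple rule for missing baseline values, such as a missing category or simple imputation. Otherwise a complete-case fit could drop participants, against Definition of populations analysed, which keeps all randomised participants in all analyses.

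The cost is wording plus that one rule, with no new data and no change in sample size. The adjusted odds ratio is conditional on the covariates and should be labelled so, because it will not equal the marginal odds ratio behind the chi-squared test.

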**Methods:**

This will be a parallel group, factorial design RCT, conducted through the English national NHS Smoking Helpline which is run from headquarters in Glasgow. Participants will be smokers who call the helpline from any location in England and who wish to stop smoking. If 644 participants are recruited to four equally-sized trial groups (total sample size = 2576), the trial will have 90% power for detecting a treatment effect (Odds Ratio) of 1.5 for each of the two interventions: i) proactive versus reactive support and ii) the offer of NRT versus no offer. The primary outcome measure for the study is self-reported, prolonged abstinence from smoking for at least six months following an agreed quit date. A concurrent health economic evaluation will investigate the cost effectiveness of the two interventions when delivered via a telephone helpline.

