### Objectives

1. To compare, amongst motivated callers to the NHS Smoking Helpline, the effectiveness and cost effectiveness of reactive and proactive quitline care for smoking cessation.

2. To compare, amongst motivated callers to the NHS Smoking Helpline, the effectiveness and cost effectiveness of, in addition to telephone behavioural counselling, two strategies for making NRT available: i) offering a voucher for free provision and ii) advising nicotine addiction treatment.

3. To investigate whether or not the provision of telephone counselling for smoking cessation via the NHS Smoking Helpline is more or less effective for disadvantaged smokers.

4. To document uptake of telephone counselling and offered NRT in trial arms.

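### A non-significant interaction test, in a trial sized only for main effects, cannot show that treatment effects are similar across deprivation; the conclusion should come from an interval, with the Townsend score kept continuous

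*Protocol article*

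**What the plan says.** Item 3 of the Objectives in the protocol article asks whether telephone counselling through the helpline "is more or less effective for disadvantaged smokers". The Background links this to smoking-related health inequalities.

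One sentence under Statistical Analysis Methods describes the analysis. It begins "We will investigate whether or not socio-economic deprivation (as measured by Townsend's score) is associated with successful outcome", says that this will be done by looking for effect modification, and ends "using a test for interaction to establish whether the effect of each treatment is similar in more versus less deprived groups". It gives no cut-point, number of groups, similarity margin or interval estimate for this contrast.

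The sample size rests on the two main effects alone. For counselling, "we will assume that proactive counselling (compared to reactive) will have a treatment effect with an OR of 1.5". For vouchers, "we will assume that the offer of NRT vouchers is also associated with a treatment effect with an OR of 1.5". The resulting claim is that "if we aim to recruit 2576 we would have 90% power to detect these differences as significant using a 5% significance level". No power is claimed for the deprivation interaction.

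**The concern.** Three features of the sentence cause difficulty.

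- **Test and question do not match.** The tool is a significance test and the stated question is similarity. A test can give evidence of a difference. Its failure to do so is evidence of similarity only if the interval is narrow, and nothing in the sizing makes it narrow.
- **Grouping.** The contrast is worded as more against less deprived groups, although the measure is a numeric score. If the score is cut, information is lost on the one contrast that objective 3 needs.
- **Two questions in one.** Whether deprivation predicts quitting is a main-effect question. Whether it changes the benefit of treatment is an interaction question. One test does not answer both.

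No other deprivation analysis is described, so objective 3 depends on this one. The risk is that an inconclusive result is taken as evidence that helpline support works equally well for disadvantaged smokers.

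**Working it through.** **Inputs from the protocol article**
- Total 2576, or 644 in each of four groups, so 1288 on each side of either main comparison.
- Odds ratio (OR) 1.5 for each treatment; 5% significance, taken as two-sided.
- Comparison and intervention rates from Table 1: 10% and 14% (validated outcome, the basis of the sample size); 14.5% and 20.3% (self-report, the primary outcome).
- Those lost to follow-up are counted as smoking, so the number analysed is not reduced.

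**Assumptions not in the article**
- Two deprivation groups, split 50:50 (30:70 as a variant), with the same comparison rate in both.
- For the coding comparison only: a normally distributed score and a linear gradient in the log OR.

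**1. The plan's own figure.** OR 1.5 applied to 8% gives 11.54%, so the comparison rate is (8 + 11.54)/2 = 9.77%. OR 1.5 on that gives 13.97%. The Fleiss formula with continuity correction at 90% power then gives 646 per trial group, against 644 stated. The main-effect sizing is therefore reproduced closely.

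**2. Interval if the observed effects are identical.** With equal halves, each treatment-by-deprivation cell holds 1288/2 = 644. The variance of the log ratio of ORs is the sum of 1/(n p (1−p)) over the four cells.
- 10% v 14%: SE = sqrt(2 × [1/(644 × 0.10 × 0.90) + 1/(644 × 0.14 × 0.86)]) = sqrt(2 × [0.01725 + 0.01290]) = 0.246. The 95% CI around 1.0 is exp(±1.96 × 0.246), or 0.62 to 1.62.
- 14.5% v 20.3%: SE = sqrt(2 × [0.01252 + 0.00960]) = 0.210. The 95% CI is 0.66 to 1.51.

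Both intervals contain 1.5 and 1/1.5 = 0.67. An observed ratio of exactly 1.0 would still be compatible with the whole assumed effect being absent in either half.

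**3. Power of the interaction test.** Power = Φ(ln R/SE − 1.96) + Φ(−ln R/SE − 1.96), where R is the true ratio of ORs. Take OR 1.5 in one half and 1.0 in the other, so R = 1.5 and ln R = 0.405.
- 10%: three cells at 10% and one at 14.3%. SE = sqrt(3 × 0.01725 + 0.01268) = 0.254, ln R/SE = 1.60, power 36%.
- 14.5%: three cells at 14.5% and one at 20.3%. SE = 0.217, ln R/SE = 1.87, power 46%.

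| Scenario | 10% | 14.5% |
|---|---|---|
| R = 1.5, 50:50 | 36% | 46% |
| R = 1.5, 30:70 (effect absent in the smaller group) | 30% | 39% |
| R = 2.0 (OR 2.0 v 1.0), 50:50 | 79% | 90% |
| R detectable with 80% power, 50:50 | about 2.0 | about 1.8 |
| Total for 80% power at R = 1.5, 50:50 | about 7,900 | about 5,800 |

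**4. Cost of a median split, if one were used.** The two halves of a normal score differ in mean by 2 × 0.798 = 1.596 SD. A ratio of 1.5 between halves therefore corresponds to a slope of 0.405/1.596 = 0.254 per SD. Expected information from the logistic model, with a mean OR of 1.5, gives:
- 10%: 54% power with a linear term, 38% with a median split.
- 14.5%: 67% and 48%.

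As a cross-check, a median split of a normal variable keeps 2/π = 0.637 of the information, so the test statistic shrinks by sqrt(0.637) = 0.798. At 10%, 54% power means a statistic of about 2.07; 2.07 × 0.798 = 1.65, which gives 38%. The split figures differ slightly from step 3 because here the ORs in the two halves lie either side of 1.5, instead of being 1.5 and 1.0.

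**The case against.** The strongest reply is that the sentence does nothing unusual. A formal interaction test is the standard way to examine effect modification, and low power for it is normal in a trial sized for main effects. The article claims no power for it. The sentence opens as an investigation, and objective 3 is two-sided. Nothing rules out reporting an interval, which a logistic interaction model would supply anyway. A condensed article may also leave the coding of a modifier to an analysis plan that is not shown.

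Much of this stands, and it limits the point in three ways.

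- A reader might infer that the plan commits to cutting the Townsend score at the median. It does not: no cut-point or number of groups is written, and the phrase could be plain language for a gradient. Grouping is the natural reading but not a certainty, so step 4 is conditional.
- A reader might infer that a non-significant result will be declared as equal benefit. The article never says so. The wording invites that reading; it does not promise it.
- A reader might infer that the test is of no use. It is not: modification as large as a ratio of 2.0 would be found with about 79% to 90% power.

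The reply does not remove the mismatch between a significance test and a question about similarity, which holds however the score is coded. Nor does it remove the merging of association with effect modification, although the mention of effect modification makes the intended analysis reasonably clear.

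**Conclusion.** The point holds as a minor improvement to the analysis of a secondary objective. It does not touch the primary analysis. At 2576 participants, non-significance could not support a statement of similarity: even identical observed effects would leave a 95% CI of 0.62 to 1.62 or 0.66 to 1.51, and complete loss of the assumed effect in one half would be missed more often than not. These figures rest on two equal groups and a common comparison rate; the 30:70 split lowers power further.

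The loss of roughly 16 to 19 points of power applies only if the score is median-split, and its size depends on a normal score and a linear gradient. The documents support saying that the method as worded is weaker than a readily available alternative. They do not support saying that dichotomisation is fixed or that a false claim of equal effect is planned.

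**What to change.** Under Statistical Analysis Methods, replace the test of similarity with estimation:

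- For each factor, fit the treatment-by-Townsend interaction in the logistic model with the score continuous.
- Report the ratio of ORs with its 95% CI. Draw the conclusion on objective 3 from that interval, and state that non-significance will not be read as equal effect.
- Report the association of deprivation with quitting as a separate result.
- Use results by deprivation group for display only.

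The cost is a few lines of analysis wording. Postcode is already among the Baseline Measures, and neither the sample size nor the follow-up changes. The change makes better use of the information available, but the interval will still be fairly wide, and the report should say so.
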